### Recruitment {15}

The intervention is delivered at the level of the district, rather than the level of the individual woman, and standard care will encompass exposure to the intervention [18].

## Assignment of interventions: allocation

### Sequence generation {16a}

The unit of randomisation in our trial is the cluster (a district), rather than individual women. Two clusters, Falaba and Bonthe, were paired before randomisation. The districts will first be allocated random area numbers, and the sequence of timing for receiving the CRADLE intervention will then be determined by computer-generated random numbers by the CRADLE statistician.

### Concealment mechanism {16b}

The districts will be masked until they are informed of their allocation four to six weeks prior to their implementation date to give sufficient time for training and distribution of devices to be arranged.

### Implementation {16c}

A new district will come on board every 6 weeks, at which point all facilities will have received their devices, and all frontline healthcare workers will have been trained in the CRADLE intervention model, as described above. This is a pragmatic trial and any deviation from the implementation plan will be recorded.

## Assignment of interventions: blinding

### Who will be blinded {17a}

The nature of the CRADLE intervention is such that blinding of women and healthcare providers cannot be achieved. However, study assignment will be masked to the CRADLE statistician and the researchers who will analyse the data.

### Procedure for unblinding if needed {17b}

The trial is not blinded; therefore, there is no unblinding procedure.

## Data collection and management

### Plans for assessment and collection of outcomes {18a}

Primary outcome data will be collected using a bespoke phone application-based electronic case report form (eCRF). District research officers were provided tablets and data allowance for this purpose. When possible, real-time online data will be uploaded directly into the eCRF, with outcomes therefore recorded directly onto the trial database. The application has been designed to have an offline function given the low availability of internet in many of SL’s rural areas. The outcomes will then upload directly into the study’s electronic database when internet becomes available.

All primary outcomes are robust and meaningful clinical endpoints that are unambiguous and therefore feasible to collect. We have chosen a composite as powering a trial for maternal death alone would require a prohibitively large sample size. We aim to demonstrate the true impact of the intervention across the health system by collecting mortality and morbidity data from hospitals and peripheral health units offering the highest level of care (20% sample. Women presenting to the peripheral health unit and referred to the hospital will be noted, to avoid double counting. Outcomes occurring elsewhere are not included.

The date at first presentation to health facility will be used to determine the period in which a woman experiencing a primary event is analysed in. For example, if a woman presents to the health facility in period one but goes on to be referred to the hospital and suffers an eclamptic fit during period two, she will be analysed within the period one cohort. This is because the district may have received the CRADLE intervention at the beginning of period two; the woman would not have been exposed to the intervention at the time of her initial presentation.

### Plans to promote participant retention and complete follow-up {18b}

Outcome data will be collected by the district research officer (DRO), with the principal investigator (PI) or a nominated deputy providing a second sign-off for all primary outcomes. Consistency and quality of source data will be monitored by the DRO at each area (ongoing). The MedSciNet database allows for extensive monitoring and query processing features, as well as a comprehensive alerting system to identify missing data. Fields including ‘limits’ will be used to avoid entry of erroneous data. The CRADLE-5 trial management team will perform a number of validation checks to verify validity and completeness. Twenty-five per cent of hospital source data will be validated by the central CRADLE team, and this will be reviewed bi-monthly during the visits by the programme manager and/or research assistant to each of the trial areas, to check for transcription errors. It will be possible to review the audit trail at individual data-point levels. Training in the trial protocol will be delivered to teams centrally (before recruitment begins) and on site in the field, to ensure staff are confident and competent to collect outcome data and quality, accuracy and completeness of data collection is ensured.

### Data management {19}

All data uploaded on the MedSciNet database will be automatically stored and backed up. Collection and storage of clinical data in the database will be governed by the UK Data Protection Act 1998. All MedSciNet data is stored on high-capacity servers that are operated by an external company. Servers are stored in locked rooms, with system monitoring 24/7, physical surveillance and surveillance cameras. A tape backup system is used for backing up the database. The MedSciNet database will remain accessible for 1 year following completion of the main trial. A copy of this will then be kept on the KCL server for 20 years following the trial completion date, in accordance with the KCL Data retention schedule. Consent forms for any qualitative aspects of the research will be kept in files in secure areas at the central site (Welbodi Partnership office, Freetown, Sierra Leone). Any personal contact information will be held on a local database kept in a locked environment, after gaining written informed consent from trial participants. Only the research assistant, the local trial project manager and the UK-based trial coordinator will have access to these. All paper documents will be stored securely and kept in confidence in compliance with the UK Data Protection Act 1998.

### Confidentiality {27}

Anonymised data will be collected by the district research officer, under the supervision of the trial coordinator. All participants will be given a unique trial identifier and no personal information will be entered into the clinical trial database or sample database. Where possible, all anonymised data will be collected directly onto the secure, online database (MedSciNet). If the low-resource nature of the environments where we will be collecting the data (e.g. very rural health clinics) means this is not possible, the data will be stored anonymously within a password protected secure phone application. This removes any need for paper-based source data collection tools and ensures confidentiality is maintained.

### Plans for collection, laboratory evaluation, and storage of biological specimens for genetic or molecular analysis in this trial/future use {33}

No biological specimens for genetic or molecular analysis will be collected during this trial.

## Statistical methods

### Statistical methods for primary and secondary outcomes {20a}

This is a type 2 hybrid implementation-effectiveness cluster randomised controlled trial in a stepped-wedge design that will allow us to simultaneously test our clinical intervention in the form of the CRADLE device and the effectiveness of our implementation strategy. This design is based on those described by Hussey and Hughes [29] and Curran et al. [30].

For our primary analysis method, we will use a new approach described by Thompson et al. [31, 32]. For this non-parametric within-period method, Monte Carlo permutation tests for stepped wedge trial designs are employed to calculate the confidence intervals and *P*-values. This is implemented in the Stata command “swpermute” [31]. Based on current statistical theory, this will provide the most accurate and reliable estimates of the intervention effect.

Thompson et al. [31] provide a non-parametric within-period method for correcting the *P*-values (and therefore the standard errors) for a valid regression model. The regression model (binomial, with a log link) that we propose to use will estimate the risk ratio for the effect of the planned intervention. It will include fixed effects for separate linear trends in each region, with a single step at the time the intervention is introduced into the district. As the method is robust to how the correlation structure is specified, further allowances for the data structure, as used in multi-level modelling, are not needed. Odds ratios will be given if models fail to converge when estimating risk ratios. Effects of treatment on primary outcomes will be estimated with 95% confidence intervals and significance at *P* < 0.05. As the primary endpoint is a composite, all the components will also be analysed in the same way. The effect of the intervention on primary and secondary outcomes will be analysed using multilevel logistic regression with random effects of centre and adjustments for fixed categorical effects of time. In addition, we will adjust for the availability of six common drugs: magnesium sulphate (MgSO_4_), ampicillin, gentamycin, metronidazole, oxytocin, and misoprostol, varying with time and district.

We have chosen a composite as powering a trial for maternal death alone would require a prohibitively large sample size. These outcomes are robust and meaningful clinical endpoints that are unambiguous and therefore feasible to collect. Improvements in these outcomes would also represent a success for the CRADLE intervention and will be presented across all districts pre- and post-intervention with adjusted risk ratios (RRs). If there are other large groups of clinically important causes of death, e.g. early pregnancy complications, these will also be defined.

### Interim analyses {21b}

All analyses will adhere to the intention-to-treat principle, meaning that subjects will be analysed based on the treatment option they were assigned to at the centre when the event occurred. No additional analyses based on the per-protocol principle will be conducted.

### Methods for additional analyses (e.g. subgroup analyses) {20b}

We will not be able to collect detailed information (for example breakdown by age or parity) on the total number of deliveries in each district so no subgroup analysis will be possible. No additional analyses based on the per-protocol principle are planned.

### Methods in analysis to handle protocol non-adherence and any statistical methods to handle missing data {20c}

We will make every attempt to get complete data in every district throughout the trial period. In the event of extreme circumstances, such as civil unrest, catastrophic weather events or major epidemic, it is possible that data collection from a specific district may not be feasible for one or more time periods. If such circumstances arise, all valid data will be analysed using the previously mentioned model.

### Plans to give access to the full protocol, participant-level data, and statistical code {31c}

The datasets used and/or analysed during the current study can be made available by the corresponding author upon reasonable request and in agreement with the research collaboration and data transfer guidelines of KCL.

## Oversight and monitoring

### Composition of the coordinating centre and trial steering committee {5d}

The trial will be supported by the Project Management Group (PMG), who includes clinical research fellows, research assistants, DROs and the CRADLE programme manager who will run programme implementation and provide organisational support, particularly to the district research officers and district health teams. The PMG will convene every month, with all co-investigators convening every 3 months to review progress, troubleshoot and plan strategically. This group will report to the trial steering committee (TSC), which is part of a bigger International Advisory Group that oversees all activities of the different workstreams of the NIHR Global Health Research Group CRIBs. The TSC will include dependent and independent members. Members will be provided with a TSC Charter and will be invited to attend, at least, annual TSC meetings.

### Composition of the data monitoring committee, its role, and reporting structure {21a}

Given the low risks of the CRADLE-5 intervention and the unlikelihood of critical safety concerns directly related to implementing the intervention, the trial will not have a data monitoring committees nor interim analysis stopping rule.

### Adverse event reporting and harms {22}

Blood pressure and pulse measurement is standard practice as a screening tool in antenatal care and therefore no adverse events or harms are expected.

### Frequency and plans for auditing trial conduct {23}

There are no additional plans for auditing trial conduct apart from those described in other sections.

### Plans for communicating important protocol amendments to relevant parties (e.g., trial participants, ethical committees) {25}

A ‘substantial amendment’ is defined as an amendment to the protocol or any other supporting document that is likely to affect to a significant degree (1) the safety or physical or mental integrity of the subjects of the trial, (2) the scientific value of the trial, (3) the conduct or management of the trial or (4) the quality or safety of any intervention used in the trial. All substantial amendments will be notified to the chief investigator, who will then notify the competent authority. Non-substantial amendments will be recorded and filed. In case amendments concern or affect participants in any way, they will be informed about the changes. If needed, additional consent will be requested and registered. Also, online trial registries will be updated accordingly.

### Dissemination plans {31a}

The results of this research will be disseminated in international peer-reviewed journals. Both positive and negative results will be reported. All attempts will be made to provide women, healthcare workers and community stakeholders a layman summary of the results within the district that were randomised to the CRADLE intervention, as well as informing government and policy makers.

## Discussion

Three quarters of maternal deaths in SL are caused by haemorrhage, hypertension and sepsis [6], all of which cause abnormalities in vital signs. The majority of deaths are preventable if deteriorating vital signs are detected early, enabling simple interventions to be delivered, which are available in SL. However, access to vital signs monitoring equipment and skilled intervention is often limited, especially in rural settings, leading to delays in escalation and delivery of care. Clinical effectiveness of introduction of the CRADLE intervention to improve maternal and perinatal health in rural areas, and integration and sustainability have yet to be investigated. This trial will evaluate whether national scale-up of the CRADLE device combined with focused training reduces maternal and fetal mortality and severe maternal adverse outcomes and will explore strategies for adoption, integration and sustainability of the intervention in Sierra Leone, which will be relevant to other low-resource settings. Developing a robust clinical trial, to address life-threatening maternal health issues, whilst taking into account the reality of the trial environment is challenging, but there is an urgent need to generate evidence specific to the local context and to evaluate interventions where they are most needed. Examples of potential limitations include capacity and engagement of district medical teams to coordinate and deliver sufficient staff refresher training, given multiple active healthcare initiatives across the country, and technical issues related to the CRADLE device, i.e. charging and broken parts, which could limit sustainable integration and impact. However, this trial design has a strong, context specific evidence base [6, 9], with substantial pilot and feasibility work, and is underpinned by several sustained collaborative partnerships in Sierra Leone, including with the MoHS. The trial protocol was developed with strong and enthusiastic in-country advocacy, with top-down and bottom-up involvement and resultant widespread acceptance of the intervention. Strong stakeholder buy-in, achieved through long-term engagement, theory of change workshops and a policy lab has led to integration of CRADLE into other programmes and initiatives including the National EmONC training package and the ‘train-the-trainer methodology galvanises local teams to take ownership at both district and community level. In summary, this intervention has been tailored for delivery to rural populations, who are amongst the most vulnerable, in terms of access to healthcare, with the worst outcomes. The study aims to generate a pragmatic, evidence-based, adaptable road map to reach, impact and empower women and healthcare workers, even in the most challenging settings.

## Trial status

The current CRADLE-5 protocol is version 1.0 (December 2022). The trial received ethical approval from the Office of the Sierra Leone Ethics and Scientific Review Committee on 24th January 2022 and from the King’s College London, UK Research Ethic Committee on 27 January 2022. The trial opened on the 23 May 2022; all outcomes occurring from 23 May 2022 to 1 January 2024 will be included in the analysis.

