## Trial design {8}

### Feasibility phase: January 2022–April 2022

The trial was preceded by a feasibility phase. The eight main trial districts collected primary outcome data to evaluate the methods of data collection and to inform the randomisation programme and sample size calculation. The results were used to optimise the final CRADLE-5 protocol including training materials and implementation strategies for the main trial.

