## Interventions

### Explanation for the choice of comparators {6b}

Prior to transitioning to the CRADLE intervention, all women will be managed according to local guidelines (see https://mohs2017.files.wordpress.com/2018/04/sl-emonc-protocols-and-guidelines-a4-final.pdf to access national guidelines for emergency obstetric and newborn care). None of the districts will receive the intervention at time point 0. One district will be randomly allocated to receive the intervention at time point 1, whilst all the remaining areas contribute to the control at this time point. A second district is randomly allocated to the intervention at time point 2 and so on. Each randomisation cluster will cross over from the control to the CRADLE intervention at six-weekly intervals (see Fig. 2).

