### Sample size estimation {14}

Sample size estimation has been provided by the CRADLE senior statistician, using Stata version 13.1 and the methods of Hemming and Girling [28]. The power of the study will depend on three factors: (1) the design (eight groups, six-weekly time periods, around 1000 deliveries/period/centre), (2) the event rate and treatment effect (5% falling to 4%) and (3) the data structure, specifically the intraclass correlation coefficient (ICC) and cluster autocorrelation (CAC) coefficients.

Sample size calculations for longitudinal cluster randomised trials, such as our proposed stepped-wedge trials, necessitate the estimation of the correlation structure underlying the study. This entails assessing both the within-period intra-cluster correlations, which differ from conventional intra-cluster correlations due to their reliance on the period, and the cluster autocorrelation coefficients to account for correlation decay. For the purposes of the power calculation, we assume that there are up to 1000 deliveries per district per six weeks (half the 2000 we consider likely), across eight districts, each observed for 12 months. It is difficult to estimate more accurately at present, as we have no suitable multi-centre, multi-time period data in a single low-income country. However, if the ICC is suitably low and the CAC is suitable high, at the time of analysis, we do not predict any difficulties. We will obtain this information from our observational pilot data gathered in January to May 2022 in all eight districts of the study. Feasibility data suggests the CAC is likely to be 1. Therefore, even with an extremely high intra-cluster correlation of 0.5, power would be close to 100%. We have used https://clusterrcts.shinyapps.io/rshinyapp/ for the calculations. As per Fig. 3, with a CAC of 1, power will be more than adequate with 1000 women per month per centre.

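### The feasibility-phase outcome rates of all eight districts are not used as a baseline, which costs much power if the primary analysis is a within-period comparison and little if the model has district-specific terms

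*Protocol article*

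**What the plan says.** The protocol article's section on the feasibility phase (January to April 2022) states: "The eight main trial districts collected primary outcome data to evaluate the methods of data collection and to inform the randomisation programme". These data also fed the sample size estimate. The sample size section dates them January to May 2022 and draws its correlation assumption from them: "Feasibility data suggests the CAC is likely to be 1".

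Under Explanation for the choice of comparators {6b}, "None of the districts will receive the intervention at time point 0". One district crosses at time point 1, so the first district to cross contributes one six-week control period.

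Trial status fixes the window: "The trial opened on the 23 May 2022; all outcomes occurring from 23 May 2022 to 1 January 2024 will be included in the analysis". The feasibility data fall before it, and no section gives a reason for leaving them out.

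Statistical methods {20a} names a within-period primary method with permutation inference for intervals and P-values ("For this non-parametric within-period method, Monte Carlo permutation tests for stepped wedge trial designs are employed to calculate the confidence intervals and"). It then gives a log-binomial regression with separate linear trends by region and a single step when a district crosses. Region is not defined there. Elsewhere the article uses the word for the country's five administrative regions. No baseline covariate is mentioned.

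**The concern.** A within-period comparison sets treated districts against untreated districts in the same six weeks. With only eight districts, a district whose rate is always high or always low shifts every one of these contrasts in the same direction, and the shift does not average out over periods. A CAC of 1, which the plan expects, means that district rates are stable. That is when this noise is most persistent and when an earlier rate from the same district predicts it best.

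The trial already holds such a rate, for the same composite and the same districts, from before any crossover. If the primary analysis is the comparison that the methods section names, its power may be far below the level the sample size section claims, and a remedy is already in hand.

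**Working it through.** **Inputs.** From the sample size section and the legend of Fig. 3: 8 districts, m = 1000 deliveries per district-period, 5% falling to 4%, CAC 1, ICC 0.01 (0.02 and 0.5 are also shown). Roll-out: time points 0 to 8, one crossover each, so 9 periods. January to April is about 17 weeks, so K = 2 to 3 six-week baseline periods. Assumed: two-sided 5% test, risk-difference scale, V = 0.045 × 0.955 = 0.042975, equal cells, and period contrasts weighted by n1·n0/(n1+n0). Power = Φ(0.01/SE − 1.96).

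**The plan's own figure first.** With district and period effects, the information left for the step is 10.5 − 42/9 = 5.833. At ICC 0.5 and CAC 1, SE² = (0.5 × 0.042975/1000)/5.833 = 3.68×10⁻⁶, so SE = 0.19 points and power = 99.9%. This reproduces the article's claim of nearly 100%, but for a model that removes district levels.

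**Within-period contrast without baseline.** At time t, t districts are treated and 8 − t are not. The weights t(8−t)/8 sum to 84/8 = 10.5. The district crossing at time i has coefficients summing to 4.5 − i, and the squares of these sums total 42. So

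SE² = (42/10.5²)·τ² + (1/10.5)·s² = 0.381·τ² + 0.0952·s².

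At ICC 0.01, CAC 1: τ² = 0.01·V = 4.30×10⁻⁴ and s² = 0.99·V/1000 = 4.25×10⁻⁵. SE² = 1.637×10⁻⁴ + 0.041×10⁻⁴ = 1.678×10⁻⁴, SE = 1.30 points, power = Φ(0.772 − 1.96) = 12%. Periods in which all districts are treated carry no weight, so the window to January 2024 does not change this.

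**With a baseline rate from K periods.** τ² is replaced by τ²·(s²/K)/(τ² + s²/K).
- K = 2: 4.30×10⁻⁴ becomes 2.03×10⁻⁵. SE² = 7.72×10⁻⁶ + 4.05×10⁻⁶ = 1.18×10⁻⁵, SE = 0.34, power = Φ(2.91 − 1.96) = 83%.
- K = 3: it becomes 1.37×10⁻⁵, SE = 0.30, power = 91%.
- Time point 0 alone (K = 1): SE = 0.43, power = 64%.

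| Setting | No baseline | K = 2 | K = 3 |
|---|---|---|---|
| ICC 0.01, CAC 1 | 12% | 83% | 91% |
| ICC 0.02, CAC 1 | 8% | 83% | 91% |
| ICC 0.005 (assumed), CAC 1 | 19% | 84% | 91% |
| ICC 0.001 (assumed), CAC 1 | 60% | 90% | 94% |
| ICC 0.01, CAC 0.8 (assumed) | 13% | 41% | 49% |

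If the paired districts (Falaba and Bonthe) cross together, giving seven sequences, the first row becomes about 12%, 81% and 89%.

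**Check by simulation.** The formula assumes an ideally scaled covariate. In 400 simulated trials per setting, with binomial data, an estimated slope and a permutation test (ICC 0.01, CAC 1), power rose from about 14-16% to 79-85%. Rejection under the null was about 4-5% with and without the covariate.

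**Models with district terms (ICC 0.01, CAC 1), feasibility periods added as control cells.**

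| Model | Periods | Power without | Power with | Variance reduction |
|---|---|---|---|---|
| District + period | 9 | 96% | 98% | 12-16% |
| District + period | 14 | 99% | 99% | 5-7% |
| District trends + step | 9 | 93% | 97-98% | 17-23% |
| District trends + step | 14 | 99% | over 99% | 15-19% |

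The 14 periods are the 84 weeks from 23 May 2022 to 1 January 2024. Seven sequences widen the ranges to about 4-19% (period effects) and 15-25% (trends). A district rate that is constant over time is collinear with district intercepts, so as a covariate it adds nothing in these models.

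**If region means administrative region.** With an assumed four regions of two districts and nine periods, the trend-plus-step regression has SE about 1.2 points and power about 13%, because district levels again stay in the error.

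**The case against.** The strongest reply is that the methods section writes out a regression, and if region there means district, that regression already removes district levels. Power is then about 93-99% at CAC 1 without any feasibility data. The section also plans a multilevel model with centre effects and categorical time, which uses change within districts. This stands, and it limits the point to the within-period contrast and to the regional reading of the regression.

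A reader might infer that the plan throws away most of its precision whatever the model, or that the main question will go unanswered. The documents do not support either. With district terms the loss is a minority of the variance, and at most about a quarter in any setting tried. Simply adding all-control periods to a within-period comparison gains nothing, because those periods contain no treated district. The gain comes only from using the earlier rate as a covariate.

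It is also fair that the feasibility phase was testing how data are collected, so keeping its outcomes out of the effect estimate is a legitimate choice. As control cells they could mislead. If ascertainment then was lower by an assumed 0.5 points, the nine-period trend-plus-step estimate shifts by −0.11 to −0.13 points, a spurious benefit against a 1-point target. The shift is near zero with 14 periods or with period effects. This does not apply to a covariate that precedes all crossovers in a randomised order: poor baseline data weaken the gain but do not bias the effect.

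Finally, Trial status does not forbid baseline adjustment, and an analysis plan that is not shown might include it. That lowers the weight of the point. But the article does fix the outcome window and describe the primary model, and neither makes use of the baseline.

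**Conclusion.** The point holds in conditional form. Under the within-period comparison that the article names as primary, power at the plan's inputs and ICC 0.01 is about 12%. A feasibility-phase covariate brings it to about 83-91% at CAC 1 and to 41-49% at an assumed CAC of 0.8. A regression with trends by administrative region leaves the same noise in (about 13% power); the covariate's gain was not computed for that model. With district-specific levels and trends, the covariate is redundant and the data left out are worth about 15-23% of the variance (about 4-16% with district and period effects), with power already high at CAC 1.

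This is a missed and cheap design gain, not an error in the document. It rests on equal district-periods of 1000, a risk-difference approximation to the log-binomial permutation analysis, the contrast weights stated above, and feasibility data of similar size and quality to trial data. The ICC is not estimated in the article; 0.01 is one of the values it illustrates.

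**What to change.** In Statistical methods {20a}, include each district's feasibility-phase composite rate (events per delivery, January to April 2022) as a covariate in the within-period permutation analysis, recomputed in every permutation with the same model. In Trial status, add that feasibility-phase outcomes are used as baseline only and do not count as trial outcomes. Report the analysis without the covariate as a sensitivity analysis. State whether region means district or administrative region, since that decides whether the covariate matters in the regression.

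Use the feasibility periods as control cells at most in a further sensitivity analysis, given the possible change in ascertainment.

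Cost: wording only, since the data exist. One extra parameter is estimated from eight districts, and a noisier baseline reduces the gain. The change should be fixed before outcome data are analysed by allocation.
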